### 2.7. Concomitant Care and Co-Intervention

Participants will continue to receive their usual oncological care throughout the study, including chemotherapy, radiotherapy, and hormone therapy. Any relevant changes in oncological treatment during the study period will be recorded as clinical variables. Participation in other structured cognitive rehabilitation or cognitive stimulation programmes during the trial will not be permitted, as it may interfere with the interpretation of intervention effects. Other standard supportive care services will be allowed and documented when relevant.

### 2.8. Participant Enrollment, Withdrawal and Adherence

Adherence to the enrollment and withdrawal guidelines will be checked by systematically recording attendance at all group sessions. A minimum threshold of 70% attendance (22 out of 32 sessions) has been established to consider the intervention complete. To maximize retention and mitigate non-attendance, the following strategies will be implemented:Automated Reminders: Notifications will be sent via WhatsApp 24 h prior to each session.Scheduling Flexibility: Session hours will be adapted to accommodate participants’ clinical and personal schedules.Group Cohesion: The intervention’s group nature is expected to foster social support, reducing the likelihood of dropout.

All absences will be documented in a systematic monitoring log using a binary system (presence/absence) and standardized coding for causes (e.g., clinical discomfort, logistical barriers, or personal reasons). While absences due to medical causes (appointments or post-treatment side effects) will be recorded for qualitative analysis, they will still be included in the final calculation of the 70% adherence threshold.

### 2.9. Withdrawal Criteria

Participants are free to withdraw from the study at any time without providing a justification and without any impact on their standard oncological care. In the event of voluntary withdrawal, the specific causes will be documented to evaluate the intervention’s feasibility.

Following the SPIRIT and CONSORT guidelines, participants who discontinue the intervention will be encouraged to complete the final follow-up assessments to facilitate an Intention-to-Treat (ITT) analysis and minimize bias due to missing data. The Principal Investigator (PI) is responsible for ensuring that all reasons for withdrawal are recorded with precision and anonymity, safeguarding data integrity for subsequent analysis.

### 2.10. Safety Monitoring and Adverse Events

The ALMA and the individual cognitive training programme are considered low-risk non-pharmacological interventions. Nevertheless, potential adverse events may include fatigue, emotional discomfort, frustration during cognitive tasks, increased anxiety related to perceived cognitive difficulties, or temporary distress during psychoeducational discussions about cancer-related cognitive impairment.

Adverse events will be monitored throughout the study period. In G2, the intervention facilitator will ask participants about discomfort or difficulties at the beginning and end of each group session. In G1, potential adverse events will be assessed during remote and in-person follow-up contacts. In G0, adverse events or relevant clinical changes will be recorded at the post-intervention assessment or whenever reported by the participant.

All adverse events will be documented in a standardized log including date, participant code, study arm, description of the event, severity, expectedness, potential relationship with the intervention, action taken, and outcome. Severity will be classified as mild, moderate, or severe. Relatedness will be classified as unrelated, possibly related, probably related, or definitely related to the study procedures. If a participant experiences clinically relevant fatigue, emotional distress, or anxiety during a session, the activity will be paused, and the participant will be offered rest, support, and the option to discontinue the session. If necessary, the participant will be referred to the appropriate oncology or psycho-oncology service according to the usual clinical care pathway.

Serious adverse events, including hospitalization, life-threatening events, or death, will be recorded and reported to the principal investigator and the relevant ethics committee according to institutional requirements. Given the clinical characteristics of the study population, adverse events related to oncological treatment will be distinguished from those potentially related to the study intervention whenever possible.

Participants will be free to withdraw from the study at any time without consequences for their standard oncological care.

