### 2.6. Intervention

#### 2.6.1. Health Education Programme G0 (Control Group)

Participants assigned to the control group (G0) will receive a standardized informational leaflet focused on evidence-based lifestyle modifications. This material will outline comprehensive instructions and recommendations for maintaining an active lifestyle, promoting self-care, and fostering healthy habits.

The content will be aligned with World Health Organization recommendations on risk reduction in cognitive decline and dementia [29]. The key areas covered in the intervention include:Nutritional optimization: Adoption of a balanced and nutritious diet.Physical & Mental Activity: Regular exercise and engagement in cognitively stimulating tasks.Psychosocial Factors: Maintenance of robust social connections and effective stress management techniques.Sleep Hygiene: Strategies for ensuring restorative and adequate sleep.Metabolic & Toxic Habits: Proper hydration, smoking cessation, and the avoidance of excessive alcohol consumption.

Strictly following the study design, this group will not receive cognitive individual or group stimulation. This group serves as a baseline comparison to evaluate the natural progression of cognitive symptoms under standard care and general health recommendations.

To capture the true, unaltered natural progression of neurocognitive symptoms under standard oncological care, the G0 group follows a passive, no-contact design between evaluations. While this limits real-time behavioral tracking, it deliberately prevents the introduction of reactive biases or artificial behavioral modifications often triggered by frequent researcher contact (the Hawthorne effect). Nonetheless, any spontaneous or clinically significant changes in participants’ lifestyle, sleep hygiene, or psychological status during this period will be captured and quantified via the multi-domain secondary psychometric outcomes (such as the PSQI and Hamilton scales) administered during the post-intervention assessment (T1).

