#### 2.6.2. Cognitive Training Group (CT) G1

Participants in the Cognitive Training (CT) group (G1) will undergo a structured programme focused on everyday cognition, administered individually to each patient. The intervention will be delivered through a meticulously developed dossier designed specifically for the objectives of this study. Notably, all participants in this arm will receive identical tasks, with no individualized adaptations for difficulty level or functional profile.

The intervention is structured into four consecutive one-month training periods (P1–P4), totaling 80 activities (20 activities per period). Participants are required to complete five activities per week. To monitor treatment adherence and ensure compliance with therapeutic guidelines, a dual follow-up system will be implemented:Remote Follow-up: Conducted via video call at the conclusion of P1 and P3 (Months 1 and 3).In-person Follow-up: Conducted at the clinic at the conclusion of P2 and P4 (Months 2 and 4) to evaluate progress and address emergent concerns.

The final evaluation for G1 will coincide with the completion of the fourth training period (P4). This group serves to control the effects of cognitive stimulation and professional monitoring without the specific multimodal components of the ALMA.

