#### 2.6.3. ALMA Group Intervention G2

The ALMA intervention is designed as a cognitive intervention programme tailored specifically for breast cancer patients. The primary objective is to address the effects of commonly known chemobrain by targeting cognitive domains commonly affected in CRCI. Beyond cognitive recovery, the programme aims to support self-esteem and patient empowerment through personalized and ecologically valid activities.

The intervention will be delivered through face-to-face group sessions at the Faculty of Psychology of the University of Salamanca. Each ALMA group will include up to six participants. If more than six participants are allocated to G2, additional groups will be created and delivered using the same intervention manual, session structure, materials, and monitoring procedures.

Group size will be limited to six participants to facilitate interaction, individualized support, and consistency in intervention delivery. The programme will span four months, with two 120 min sessions per week, resulting in a total of 32 sessions. The ALMA intervention is characterized by the following components:Targeted Cognitive Stimulation: Structured exercises focusing on memory, executive functions, attention, language, and mathematical/logical reasoning with dynamic adjustments to address specific patient deficiencies.Neuro-education & Health Literacy: Integrative discussions on neuroscience, cognitive health, and overall well-being to foster self-management.Group Dynamics: A collaborative environment designed to facilitate social support and emotional resilience among peers.

The activities will be adaptively tailored to the participants’ functional profiles, ensuring that the stimulation is both accessible and clinically relevant.

To ensure the replicability of the ALMA intervention, the operational components, session structure, materials, and monitoring procedures will be standardized and described in detail in Supplementary Material S1.

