Non-blinded investigator: A notable methodological constraint of this protocol pertains to the absence of a blinded evaluator for the neuropsychological tests. This is due to the fact that the same professional responsible for the initial and final assessments is also the one who conducts the ALMA group interventions. This arrangement, motivated by resource optimization and the need to maintain a consistent therapeutic relationship with the participants, could introduce detection bias or researcher expectations bias in the administration of the post-intervention instruments. Nevertheless, a range of strategies will be implemented to mitigate this risk and safeguard the integrity of the findings. These include standardizing assessment instruments, implementing statistical analysis without the researcher’s knowledge, ensuring that participants are unaware of the hypothesis, and utilizing robust modeling (LMM).

Additionally, to prevent subconscious cueing or expectancy effects during post-intervention (T1) evaluations, a rigid behavioral protocol will be enforced. This includes the strict use of manualized verbatim scripts for all test administrations to ensure identical phrasing, the systematic maintenance of a neutral affective posture (suppressing non-verbal reinforcements such as nodding or smiling, and avoiding differential verbal praise), and the use of precise digital timers to govern all response windows objectively, thereby completely eliminating investigator discretion.

Attrition Risk: The nature of the population (patients in active oncological treatment) poses a risk of dropout due to medical complications, fluctuating health status, or scheduling conflicts. While retention strategies are in place, high attrition could impact the statistical power of the final analysis.

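### The adverse-event routes in Section 2.10 depend on attendance or self-report and differ by arm, and no attendance-independent source is named for serious events, so counts by arm may be incomplete and not comparable

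*Protocol article*

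**What the plan says.** Section 2.10 undertakes to monitor adverse events over the whole study and then sets a route for each arm.

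- **G2:** "In G2, the intervention facilitator will ask participants about discomfort or difficulties at the beginning and end of each group session".
- **G1:** "In G1, potential adverse events will be assessed during remote and in-person follow-up contacts". Section 2.6.2 fixes these as two video calls (Months 1 and 3) and two clinic visits (Months 2 and 4).
- **G0:** "In G0, adverse events or relevant clinical changes will be recorded at the post-intervention assessment or whenever reported by the participant". Section 2.6.1 adds that "the G0 group follows a passive, no-contact design between evaluations".

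Serious events have their own sentence, not limited to any arm: "Serious adverse events, including hospitalization, life-threatening events, or death, will be recorded and reported to the principal investigator and the relevant ethics committee", in line with institutional requirements. It does not say how the trial team learns of such an event.

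Section 2.11 gives the oncology team the task of identifying candidates and states no safety-reporting role for it. It also rules out an independent data monitoring committee. Section 6 accepts that active oncological treatment "poses a risk of dropout due to medical complications, fluctuating health status, or scheduling conflicts".

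**The concern.** Every route described needs the woman to attend, to be reachable or to make a report herself. A G0 woman who dies, or is too ill for T1, meets neither of the two G0 routes. A G2 woman who stops attending is no longer asked the session questions, and Section 2.10 does not name T1 as an enquiry point for her. The women whose events matter most are therefore the least likely to be reached, and the degree of dependence on attendance differs by arm.

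Serious events should be the part of the harms record least sensitive to how often participants are questioned. That makes them the most useful between-arm description of harm in an open-label trial without a monitoring committee. The advantage is lost if they too are found through contact that differs by arm. Late discovery also delays reporting to the ethics committee, and the reason for a missing T1 in G0 may stay unknown, which bears on the missing-at-random assumption in Section 3.9.

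**Working it through.** The plan states no serious-event rate or capture rate, so there is no figure to reproduce. The check counts the enquiries that follow from the stated rules, sets the other records beside them, and then illustrates what incomplete capture would do.

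**1. Scheduled adverse-event enquiries per woman**

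- G2: Section 2.6.3 gives a programme "with two 120 min sessions per week, resulting in a total of 32 sessions". Two enquiries per session give 32 × 2 = 64. At the 22-session adherence threshold, 22 × 2 = 44.
- G1: 2 video calls + 2 clinic visits = 4.
- G0: 1 (T1), plus whatever the woman reports unprompted.

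**2. Intervals without a stated enquiry**

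- The programme lasts 32 / 2 = 16 weeks.
- A G2 woman who stops after session 10 (week 10 / 2 = 5) has 16 − 5 = 11 weeks with no stated adverse-event enquiry, although her absences are coded.
- A G0 event soon after randomisation may wait about 16 weeks for the first scheduled enquiry. If T1 is missed, there is none.

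**3. Women likely to miss T1**

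Section 2.4 anticipates about 10% attrition: 63 × 0.10 = 6.3 women, or 21 × 0.10 = 2.1 per arm if spread evenly. This counts women without T1. It is not a count of serious events.

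**4. Do the other stated records close the gap?**

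- Absence codes (Section 2.8) cover group sessions, so G2 only, and serve adherence.
- Withdrawal reasons (Section 2.9) are documented, but no justification is required of the woman, and death or incapacity is not voluntary withdrawal.
- Women who stop the intervention are encouraged to attend T1 (Section 2.9). That does not reach those too ill to come.
- Relevant treatment changes are recorded in all arms (Section 2.7), with no source named; a death or admission need not appear as one.
- Internal monitoring (Section 2.11) reviews adverse-event reports and completeness of assessments. It reviews what has been collected.

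Each helps in part. The most frequent one, absence coding, exists in one arm only.

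**5. Illustration under assumptions**

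Let p be the true risk that a woman has a serious event and c the share captured in G0. Neither is in the document. Expected women with an event per arm = 21p; chance of at least one = 1 − (1 − p)^21; expected number missed in G0 = 21p(1 − c).

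| Assumed p | Expected per arm | P(at least one) | Missed, c = 90% | Missed, c = 75% | Missed, c = 50% |
|---|---|---|---|---|---|
| 5% | 1.05 | 0.66 | 0.11 | 0.26 | 0.53 |
| 10% | 2.10 | 0.89 | 0.21 | 0.53 | 1.05 |
| 20% | 4.20 | 0.99 | 0.42 | 1.05 | 2.10 |

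If capture is complete, nothing is missed. Over this grid the expected shortfall in G0 runs from about 0.1 to 2.1 women, against expected totals of 1 to 4 per arm.

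**The case against.** The best defence is that serious events have a commitment of their own, covering all arms and not limited by attendance. The G0 sentence concerns adverse events generally, and silence about a source does not confine collection to attenders. The article condenses a fuller protocol, and how serious events reach the investigator is often left to that document or to institutional procedure. G1 has a clinic contact at Month 4, which coincides with its final evaluation. In G2 the person who runs the sessions also carries out T1. All participants stay under the care of the department where the trial is run. Section 3.9 plans no between-arm test of serious events, and with 21 women per arm any such comparison would be imprecise.

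Much of this stands. A reader might infer that serious events are collected only from attenders, that a woman who dies or stops attending drops out of the safety count, or that totals by arm will be wrong. The document supports none of these: the all-arm commitment is there, partial routes exist, and no text removes anyone from a count.

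The arm-specific rules themselves are not answered. They are stated, not left to another document; they rest on contact; and they do not sit easily with the promise of monitoring throughout the study in an arm that is deliberately left uncontacted.

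**Conclusion.** The point holds in a limited form. Followed as written, Section 2.10 gives adverse-event ascertainment that depends on attendance or self-report and differs sharply by arm (up to 64, 4 and 1 scheduled enquiries). The commitment on serious events is sound but has no stated source independent of attendance. Serious events in women who miss T1 or stop attending, especially in G0, may be found late or not at all, so counts by arm may be incomplete and not comparable.

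The size of any error cannot be derived from the document. The shortfalls in the table rest wholly on assumed risks and capture rates, and the figure of about two women per arm without T1 rests on the planned attrition being spread evenly. The conclusion would weaken if the full protocol or institutional procedure already provides a uniform record check. The change is worth making before recruitment, but the primary efficacy analysis does not hang on it.

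**What to change.** State in Section 2.10 that, at the planned T1 date, the oncology team checks the hospital record of every randomised woman in all three arms, whether or not she attended. The check covers death, life-threatening events and hospitalization since randomisation. Report serious events by arm over all 63 randomised women for that fixed window, and keep events found through the arm-specific routes in a separate description. Confirm that the consent form covers this record access, including for women who have stopped the intervention.

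The cost is about 63 record checks by a team already involved in the trial and, if needed, one sentence in the consent form. G0 stays free of research contact and no clinical management changes. Admissions to other hospitals may still be missed, but this limitation applies to all arms. A single check at T1 makes the count uniform; it does not by itself make reporting during the four months any quicker.

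### Adverse events are asked about on three different schedules, so any by-arm count of mild, transient events is expected to be inflated for ALMA

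*Protocol article*

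**What the plan says.** Section 2.10 gives each arm its own rule.

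- **G2 (ALMA):** "In G2, the intervention facilitator will ask participants about discomfort or difficulties at the beginning and end of each group session". Section 2.6.3 sets the exposure at "two 120 min sessions per week, resulting in a total of 32 sessions", and Section 2.8 adds: "A minimum threshold of 70% attendance (22 out of 32 sessions) has been established to consider the intervention complete".
- **G1 (cognitive training):** "In G1, potential adverse events will be assessed during remote and in-person follow-up contacts". Section 2.6.2 lists two video calls (months 1 and 3) and two clinic visits (months 2 and 4), and places the final evaluation at the end of the fourth period.
- **G0 (health education):** "In G0, adverse events or relevant clinical changes will be recorded at the post-intervention assessment". The sentence goes on to admit events that a participant reports on her own initiative. Section 2.6.1 states that "the G0 group follows a passive, no-contact design between evaluations".

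All events go into one standardized log that records study arm, severity, expectedness and relationship to the intervention. Section 2.10 names T1 as an enquiry point only for G0. It gives no question or time point shared by the three arms, and no rule separating events by how they were elicited.

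**The concern.** The non-serious events that Section 2.10 anticipates include tiredness, frustration, anxiety and passing distress. Many of these are short-lived, so whether one is recorded depends on how soon and how often the woman is asked. Section 1 itself says that fatigue and distress may be particularly relevant during active treatment, so background events of this kind can be expected in every arm, including the arm that receives only a leaflet.

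The question also differs. G2 is asked about discomfort or difficulties, which is broader than the G1 enquiry about potential adverse events or the G0 wording about adverse events and relevant clinical changes. Frequency and breadth push in the same direction.

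Two misreadings are then possible. ALMA may appear to cause more minor harm than the comparators when it does not, or a real excess may be set aside as the product of more frequent asking. The log cannot tell these apart. Grading relatedness, or separating events due to cancer treatment, classifies events after they have been detected; it does not make detection equal. This rule is fixed at data collection, and no later analysis can recover events about which nobody asked.

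**Working it through.** **Step 1. The plan's own session count.** Two sessions per week over 16 weeks (taking four months as four 4-week months): 2 × 16 = 32. This reproduces the stated total.

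**Step 2. Scheduled enquiries per woman.**

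| Arm | Source | Count |
|---|---|---|
| G2, full attendance | 2 per session × 32 sessions | 64 |
| G2, at attendance threshold | 2 × 22 | 44 |
| G1 | 2 video calls + 2 clinic visits | 4 |
| G0 | T1 only, plus self-reports | 1 |

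The G1 final evaluation coincides with the month 4 contact, so it adds no fifth time point. The ratios at full attendance are 64/4 = 16 (G2 to G1) and 64/1 = 64 (G2 to G0). These are ratios of asking, not of events.

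**Step 3. A simple illustration of the effect on counts.** Assume equal true rates, and let r be the share of session-captured events that a single T1 question recovers. The apparent G2 to G0 ratio is 1/r. With r = 0.7 it is 1/0.7 = 1.4; with r = 0.3 it is 1/0.3 = 3.3. The documents give no value for r, so this range is an assumption.

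**Step 4. A cross-check that also covers G1 and self-reports.** Assume equal true rates, events spread evenly over 16 weeks, and a probability exp(−lag/τ) that an event is reported at the next enquiry. For enquiries L weeks apart, the share captured is (τ/L)(1 − exp(−L/τ)). Use L = 0.5 for G2 (each session counted once, which is conservative), 4 for G1 and 16 for G0.

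| τ (weeks) | G2 | G1 | G0 | G2:G0 | G2:G1 |
|---|---|---|---|---|---|
| 2 | 0.885 | 0.432 | 0.125 | 7.1 | 2.05 |
| 4 | 0.940 | 0.632 | 0.245 | 3.8 | 1.49 |
| 8 | 0.969 | 0.787 | 0.432 | 2.2 | 1.23 |

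If a share s of missed events is volunteered in every arm, the captured share c becomes c + (1 − c)s. With s = 0.5 and τ = 4, G2 is 0.940 + 0.060 × 0.5 = 0.970 and G0 is 0.245 + 0.755 × 0.5 = 0.623, a ratio of 1.56. Over τ = 2 to 8 with s = 0.5, G2:G0 runs from 1.7 down to 1.4, and G2:G1 from 1.3 down to 1.1.

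**Step 5. What this would look like in the log.** With 21 women per arm and an assumed 2 true events each (42 per arm), τ = 4 and no self-reports, the log would hold about 42 × 0.940 = 40 events in G2, 42 × 0.632 = 27 in G1 and 42 × 0.245 = 10 in G0, with no true difference.

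The direction is the same in every scenario. The size depends on τ, s and r, none of which the documents give.

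**The case against.** The strongest reply is that the plan promises no comparison that this could bias. Adverse events are not among the outcomes in Section 3 or Table 3, Section 3.9 plans no by-arm test of them, and recording the arm in a log is ordinary record-keeping. Tabulation may be settled in an analysis plan that is not shown. That stands as a limit on the consequence. It does not answer the point about collection: an analysis plan can separate events by source, but it cannot supply a like-for-like enquiry that was never made.

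Several further points stand and narrow the concern:

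- G0 has a self-report route, which reduces the gap without closing it (Step 4).
- Some anticipated events, such as frustration with tasks or distress in psychoeducation, cannot arise from study procedures in an arm that receives a leaflet. For these, equal true rates is the wrong starting assumption, and part of a higher G2 count would be genuine.
- Asking at each session protects participants and fits the pause, rest and referral steps in the same section.
- Hospitalization, life-threatening events and death depend much less on prompting.
- The Hamilton scale and PSQI are given at T0 and T1 in every arm, so anxiety and sleep have an even comparison outside the log. Fatigue, frustration and passing distress have no comparable common measure.

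Sections 4.1 and 6 acknowledge unequal contact, but as an influence on participants' outcomes, not on the detection of adverse events.

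**Conclusion.** The concern holds in a limited form. Scheduled enquiry is up to 64 times per woman in G2, four in G1 and one in G0 plus self-reports, with different wording and no common question. Any by-arm count of mild, transient, non-serious events from the single log is expected to be inflated for ALMA relative to both other arms. Against G0, an illustrative range is 1.4 to 3.3 times if one T1 question recovers 30% to 70% of session-captured events; the decay model gives 1.4 to 7.1 depending on memory and self-report. All of these sizes rest on assumptions.

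A reader might infer that the log is certain to show harm from ALMA where there is none, or that the trial could not support its low-risk description at all. The documents do not support either. Inflation is an expectation of unknown size, no by-arm test is planned, and serious events and the Hamilton and PSQI comparisons remain informative. Low risk is also a design premise, used in Section 2.11 to justify having no independent monitoring committee; it is not a hypothesis that the trial sets out to test. The point is an inexpensive improvement to harm reporting and does not affect the primary or secondary outcomes.

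**What to change.** Amend Section 2.10 as follows.

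1. Keep the G2 session prompts and G1 contact prompts for participant protection.
2. At T1, give all three arms the same structured adverse event checklist with the same recall window.
3. Base any between-arm comparison of non-serious events on that checklist only.
4. List session-elicited (G2), contact-elicited (G1) and spontaneously reported events separately by source, without comparing arms.
5. Continue to report serious adverse events by arm from all sources.

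The cost is a few minutes at a visit that already takes place and a few sentences of text; G0 keeps its no-contact design. With one common enquiry, the scheduled count for the comparison becomes 1:1:1. Two weaknesses remain and should be stated: the checklist will miss some short-lived events over a recall period of about four months, and women who have been questioned repeatedly may still recall or label events more readily than G0 women.
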